**SECTION C – DESCRIPTION OF THE RISKS AND BENEFITS OF THE PROPOSED RESEARCH**

1. What are the proposed benefits to the participants, the scientific community or society that would justify asking individuals to participate?

Society - Sarcopenia is indirectly responsible for many age related morbidities such as falls and bone fractures, muscle weakness a loss of functional independence. Resistance exercise is an effective countermeasure to sarcopenia, however, there are issues of poor long-term compliance. Substances that can enhance the effects or resistance exercise or work in isolation would be of immense benefit to older adults with sarcopenia and also for healthy older adults (such as in the current proposal) to prevent sarcopenia.

Individual – Each participant will have an exercise stress test, a nutritional assessment and body composition analysis (including bone density). These test results are of interest to many people and may identify aspects of health that need preventative attention such as low bone mineral density. 50 % of the participants will have supervised exercise training for one year (~ 150 – 400 dollar benefit, depending on the health club). All participants will be taught a stretching program. At the end of the study, any of the people in the non-exercising program will be offered a two session supervised instruction period to help them get starting in and exercise program if they desire.

Scientific Community – There will be a number of outcome variables that will answer important questions about aspects of muscle adaptation to exercise. An example is the hypothesis that satellite cells may function as stem cells and bring non-mutated mitochondrial DNA into the muscle fibers that can alter the ratio of mutated mitochondrial DNA (deletions) toward a younger profile.

1. Specify the risks to participants involved in this study [e.g. physical risks (pain, discomfort, injury, side effects), psychological risks (participants feel demeaned, worried, upset, embarrassed), social or economic risks (invasion of privacy or breach of confidentiality).

- Creatine has been used by millions of athletes throughout the world for over 5 years. There is one report of an individual with pre-existing renal disease who showed an apparent worsening of kidney function while supplementing and another report of interstitial nephritis in a young man taking twice the recommended maximal dose for 1 month. Because of these case reports we will be conservative and exclude those with known or the potential for (i.e., diabetes) kidney disease. There have been 2 longitudinal studies using creatine for > 1 month and neither has shown any significant adverse effects. All blinded trials that have measured renal function have not shown any deterioration. There have been some anecdotal reports of stomach cramps, however, this appears to be related to the consumption of un-dissolved powder in a minority of subjects. There have been 3 prospective trials in older adults (> 65y) with exercise training and creatine interventions with no reported side effects. We found no evidence of subjective side effects nor alterations in renal and hepatic function in our 4 month trial in older adults (Brose, et al.,  *J Gerontol A Biol Sci Med Sci.*, 58:B11-9, 2003).
- CLA. There have been no reports of adverse effects from CLA in any human studies and it is important to note that CLA is an essential fatty acid found naturally in products such as milk (Blankson, et al, ). The amount of fat from the CLA is about 5 % of the total dietary fat intake.
- Muscle biopsy. A muscle biopsy will be taken before and after the training from the *Vastus lateralis* (outer leg) muscle. [name] has performed over 10,000 of these in patients and healthy control subjects ranging in age from 1 week to 90 y. with the following complications:
- 4/10,000 with a local skin infection.
- 6/10,000 with a fibrous lump at the site of biopsy (connective tissue); all disappeared with massage after < 1 week.
- 4/10,000 with a small patch of numbness just past the biopsy incision (size of a quarter) due to cutting a small sensory nerve branch. In all cases complete recovery occurred in < 3 months.
- The muscle usually has a dull ache for 24-48 h (markedly reduced with ice and mild analgesics such as Tylenol or Advil).
- In theory, one could damage a small motor branch of the m. *Vastus lateralis* and partially weaken the lower aspect of the muscle. This should not affect function for this muscle is only one of the four that have a role in knee extension. However, it has not been observed in any of the patients biopsied by [name].
- DEXA Scan: A DEXA scan is the most accurate measurement of body fat mass currently available. It uses a very low intensity radioactive beam to measure the amount of muscle and fat. The amount of radiation exposure is less than a cross-Canada airplane flight and much less than a standard chest X-ray (> 10 X less). There are no known risks with this test.
- Blood sampling. A single needle stick (Venipuncture) will be used to take blood three times during the study (pre-, mid- and post-test). The possibility of a small bruise at the site exists. The total amount of blood taken at any time is going to be 15 ml, which should have no negative effects.
- Muscle Testing/Training: Muscle strength testing may pose some risk for ligamentous or tendon injury. Knee extension strength is a standard testing and training method used in the elderly. In the last study that we completed in older adults (N = 28), there were no reported injuries from the testing or training. There are a number of these persons still participating in the “Seniors Exercise Program”.
- Exercise stress testing. We will not allow participants with abnormal resting ECGs or a blood pressure of > 160 mmHg systolic and/or 95 mm Hg diastolic to complete the exercise protocol (Bruce). It has been determined that the risk of a cardiac event during such testing is about 1/100,000. Subjects will feel tired at the end of the study and possibly light headed.

1. How will you manage and minimize the risks?

- Muscle Testing/Training: The training program that we have devised (see also Brose, et al.,  *J Gerontol A Biol Sci Med Sci.*, 58:B11-9, 2003), starts with low weights and gradually progresses as the individual adapts to the program. There is a light warm-up before each testing and training session. Any reports of tendon/ligament pain will be assessed by one of the supervising physicians and appropriate external consultation sought if it does not resolve with minor interventions.
- Serum CK activity, bilirubin, gamma-glutamyl transferase (GGT), and creatinine will be taken pre-, at 6 months, and at the end of the study. The pre- and + 6 month values will be provided to two local staff physicians (gastroenterologist and cardiologist) who will review the data and determine if there are any alterations that require further investigation or withdrawl from the study.
- Exercise stress testing. Prior to starting the study, each participant will have a symptom limited exercise stress test completed to determine maximal oxygen consumption and to determine if there are any ECG abnormalities. Any abnormalities that are deemed to be a risk to participation in an exercise program will be used as an exclusion criteria and the family doctor will be provided with the test results for appropriate action. [name] will review the pre-study and + 6 month tests for study exclusion or study withdrawal at the 6 month testing period. A defibrillator will be on hand at the time of the testing and each subject will have a 12 lead ECG.
- General health risk. Each participant will complete a health questionnaire and will be screened by the research coordinator to ensure that there are no contra-indications to participation. The family doctor of each potential candidate will be contacted to determine whether there are any contra-indications to participation. Specific exclusion criteria will include: known coronary artery disease, congestive heart failure, renal failure, diabetes requiring insulin or > 5 mg Glyburide or equivalent, renal failure (creatinine > 120, potassium > 5.00 mmol/L), previous stroke, uncontrolled hypertension or hypertension requiring more than mono-pharmacotherapy, inability to consent due to cognitive difficulties, chronic obstructive pulmonary disease (FVC or FEV1 < 85 % of age predicted mean value or requiring any medication other than a puffer as needed) or joint related problem that would exclude them from performing the strength training. Furthermore, we shall exclude persons who have a hip or lumber spine bone mineral density that is > 2 SD below the age adjusted mean values (based upon the DEXA scan).

1. (a) Will participants be reimbursed for expenses? [X] YES [ ] NO

If YES, please provide amount(s) and item(s) covered.

Participants will be reimbursed for their time commitment to the study for testing and follow-ups and for travel to and from the McMaster campus (or parking, if applicable). The estimated cost is about and this will be provided to each participant (extra will not be given to those randomized to exercise for this supervised training is inherently valuable (see below and above)).

(b) What other inducement or compensation is offered to participants?

The strength testing, diet assessment, VO2max testing, and body composition are all variables of interest that some people pay for at health clubs.

All participants will be given supervision on a daily stretching program before and again at 6 months.

The 50 % of people who will exercise will also benefit by the fact that they will have free, supervised exercise training. The 50 % who will not be exercising will be taught a stretching program and will come in to the center every 2 weeks to review this and complete the stretches as part of a group.

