  2. In our pilot study we had a drop-out rate of 7 %, and if we assume a drop-out rate of twice this (~ 6/group), we should retain 34 people at each of the two centers with 34 in RT and 34 on the combined supplement.

1. Design/Methodology:

Participants who are deemed eligible to participate will be randomly allocated into one of four groups. The allocation will be based upon an expected equal recruitment at the London (total = 40) and Hamilton (total = 40) sites and there will be 10 independent blocks of 4 randomly distributed interventions at each site (20 allocated to strength exercise (10 = + supplement; 10 = no supplement) and 20 allocated to no exercise (10 = + supplement; 10 = no supplement)) with an equal distribution:

1. Resistance training (RT) (12 months, 3dwk-1) and placebo (PL) – Group = RT + PL.

2. RT as in # 1 + CrM (5 gd-1) and CLA (3 gd-1) supplementation (SUPP) – Group = RT+SUPP.

3. Sedentary (12 months of home stretching (SED)) and placebo (PL) = SED.

4. SED as in # 3 + SUPP as in # 2 – Group = SED+SUPP.

1. Setting (e.g. outpatient, ICU, community):

The participants will be healthy ambulatory community dwelling men and women over the age of 65 y.

a. Exercise testing – Rm 4U18 and 2F MUMC (Neuromuscular research testing area – [name]).

b. Exercise training – Tue and Thur. – Ivor Wynne Center exercise center.

1. (a) Brief description of participants:

Men and women over the age of 65 y and less than 85 y who are living independently in the community with no contra-indications to exercise testing or training will be recruited.

(b) Are there any age, ethnicity, language, gender or race-related inclusion or exclusion criteria? [ ] YES [ X ] NO

If YES, please justify:

We plan to recruit equal numbers of men and women.

1. Study interventions:

a) Exercise training (50 % of recruits; other 50 % will continue with their usual routine) – participants will perform supervised strength/resistance exercise three times a week (Tue/Thur) for **12 months** using a machine based whole body exercise program that we have shown previously to be safe and effective (Brose, et al.,  *J Gerontol A Biol Sci Med Sci.*, 58:B11-9, 2003). Subjects will also perform a home based exercise routine on Saturday with rubber bands and resistance exercises not requiring weights (i.e., sit-ups).

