b) Nutritional supplement (50 % of recruits; the other 50 % will consume a placebo (nested within the exercise and sedentary groups) – the supplement will consist of 3 g/d of conjugated linoleic acid and 5 g/d of creatine monohydrate for **12 months**.

1. Primary outcome(s) (***“What”*** will the study measure?):

The following measurements will be completed before (pre), at 6 months, and again at the end (+12 months) of the study:

a) Muscle and bone mass.

b) Functional capacity.

c) Knee extension strength.

d) Strength with weight training machines.

e) Muscle fiber area and creatine content.

f) Muscle oxidative capacity.

g) Aerobic power (oxygen consumption).

1. Measurements (***“How”*** will the study measure it?) and plan for data analysis:

a) Muscle and bone mass – DEXA scanning.

b) Functional capacity – stair climb, get up and go and walking test.

c) Knee extension strength – isometric dynamometery.

d) Strength with weight training machines – peak strength in 8 muscle actions.

e) Muscle fiber area and creatine content (muscle biopsy pre and post only) – ATPase staining and enzymatic biochemistry.

f) Muscle oxidative capacity (muscle biopsy pre and post only) – electron transport enzyme activity - biochemistry.

g) Aerobic power (oxygen consumption) – VO2max test + 12 lead ECG on cycle ergometer.

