Subjects who withdraw prior to randomization or within the first week (i.e., before the first testing session) will not be considered to have started the study and will be thanked for their interest. There are a few individuals who may use the study as a vehicle to obtain free exercise training and may drop out if they are not randomized to the exercise group. In our experience, this is about 5 – 10 % of all persons and we will notify people whether they are in the exercise groups or not before the first testing session. Once in the study (i.e., after the first testing session) all drop-outs will be considered in an intention to treat analysis of the data and the reason for the withdrawal will be noted and will be part of the final manuscript. Participants who experience any side effect from the study (i.e., tendonitis from exercise training) will be covered for the costs of treatment (such as physiotherapy or anti-inflammatories) and if they drop-out because of a negative consequence of the study, they will be given the full remuneration.

1. Will you be contacting participants either by telephone or letter during the project? [X] YES [ ] NO

If YES, append a copy of the telephone script or list of questions with the research protocol.

Participants will be contacted by telephone to book times for their testing sessions in order to fit into their schedule.

“Hello, this is ____________ calling from the older adult training study. We would like to plan the times for your testing sessions. We have a number of open testing sessions available including, ………… dates. If none of these times is convenient for you, are there times that would be more appropriate for you? Do you know how to get to the McMaster Medical Center, if not, we can send you a map or explain it over the phone. Thank you for participating in the study and we look forward to seeing you on (time and date).”

If participants miss more than one exercise session, they will be contacted to see if there is anything wrong (i.e., are they ill, injured, still interested in participating?).

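### Section C lets 6-month safety reviewers withdraw randomised people from the study itself, and nothing provides for their 12-month outcomes, although Section D promises an intention-to-treat analysis of all drop-outs

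*Protocol*

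**What the plan says.** Section C of the protocol, on managing and minimising risks, gives two routes out of the study at 6 months. Two staff physicians look at CK, bilirubin, GGT and creatinine and "determine if there are any alterations that require further investigation or withdrawl from the study". Separately, a reviewer of the exercise stress tests "will review the pre-study and + 6 month tests for study exclusion or study withdrawal at the 6 month testing period". Neither sentence mentions stopping only the training or only the supplement.

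Section D, on procedures for people who withdraw, says of participants already past their initial testing that "all drop-outs will be considered in an intention to treat analysis of the data and the reason for the withdrawal will be noted". Beyond that it deals with publication of the reasons, treatment costs and remuneration.

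Section B, Part II, says that the outcome measurements "will be completed before (pre), at 6 months, and again at the end (+12 months) of the study". The measurement list then restricts the biopsy outcomes. One entry reads "Muscle fiber area and creatine content (muscle biopsy pre and post only", and the entry for muscle oxidative capacity carries the same restriction.

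The point uses the 12-month duration of Section B. The opening summary gives 8 months, but the 6-month review comes before the final assessment on either figure.

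**The concern.** An intention-to-treat analysis needs outcomes on the people randomised, including those who stopped treatment. Withdrawal from the study, in its ordinary sense, ends measurement as well as treatment. The protocol therefore promises to analyse everyone as randomised while allowing some of them to leave before the final measurement.

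The decision rests on results obtained after randomisation, and some of these may depend on the arm. The protocol treats kidney function as a safety question for creatine, and creatinine is one of the values reviewed. For the stress test, the stated pre-study standard is risk to taking part in an exercise programme. If that standard is carried over to 6 months, which is an inference, it bears more directly on the training arms than on the stretching arms. Unequal loss of this kind can bias the comparison of those who remain.

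A statistical analysis plan can say how missing values are modelled. It cannot recover measurements that were never taken, so whether withdrawn people are still measured is a matter for the protocol.

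**Working it through.** **1. What a person withdrawn after the 6-month tests contributes, on a plain reading**

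| Outcome | Baseline | 6 months | 12 months |
|---|---|---|---|
| DEXA, function, strength, aerobic power | yes | yes | none |
| Fibre area, creatine content, oxidative capacity (biopsy) | yes | not planned | none |

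For the biopsy outcomes, no value after randomisation remains.

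**2. The plan's own figure on loss**

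Section B, Part II, starts from the pilot ("In our pilot study we had a drop-out rate of 7" per cent) and doubles it ("if we assume a drop-out rate of twice this (~ 6/group"). Per 40 people, 40 × (1 − 2 × 0.07) = 40 × 0.86 = 34.4 retained and 5.6 lost. The protocol states 34 and about 6, so the figure is reproduced. It covers drop-out for any reason. No rate is given for withdrawal ordered by a reviewer.

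**3. Possible bias in one arm's completer mean**

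Let w be the share of one arm withdrawn, m the mean change of those who complete, and g the shortfall of the withdrawn in SD units. The mean of all randomised is (1 − w)m + w(m − g × SD) = m − w × g × SD, so completers overstate it by w × g × SD. (If the withdrawn would have done better, the sign reverses.)

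The SD of 25.5 Nm and the difference of 28 Nm come from the knee-extension calculation in Section B, Part II. Both w and g are assumptions. With 40 people on each side of a pooled comparison, w = 2.5% is 1 person and w = 15% is 6, which is the whole drop-out allowance.

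| w | g = 0.5 | g = 1 |
|---|---|---|
| 2.5% | 0.32 Nm (1.1% of 28) | 0.64 Nm (2.3%) |
| 5% | 0.64 Nm (2.3%) | 1.28 Nm (4.6%) |
| 10% | 1.28 Nm (4.6%) | 2.55 Nm (9.1%) |
| 15% | 1.91 Nm (6.8%) | 3.82 Nm (13.7%) |

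The protocol's printed formula inserts an SD of 20 instead of 25.5. With 20, the ends of the range are 0.025 × 0.5 × 20 = 0.25 Nm and 0.15 × 1 × 20 = 3.0 Nm (0.9% and 10.7% of 28).

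**4. Effect on power**

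Power = Φ(Δ / (SD × √(2/n)) − 1.96), two-sided 0.05, with Δ = 28 and SD = 25.5. For n = 40 this is Φ(28/5.70 − 1.96) = Φ(2.95) = 0.998.

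- Pooled comparison: 0.998 with 40 per side, 0.995 with 34, 0.989 with 30, 0.977 with 26.
- Single groups: 0.935 with 20, 0.893 with 17.
- Fat-free mass (1.39 kg, SD 0.68): rounds to 1.00 throughout.

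The pooled figures assume that the pilot difference, seen in people who trained, holds for the whole comparison. On these inputs the issue is possible bias, not lost power.

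**The case against.** The strongest reply is that Section C sets no automatic removal. The blood reviewers may ask for further investigation instead, and both rules leave the decision to case-by-case judgement. The text never says that 12-month tests are cancelled. It comes from an ethics form, where withdrawal from the study may be loose wording for stopping the intervention. The protocol's own evidence also suggests few cases: it reports no change in renal or hepatic function in the 4-month trial, no deterioration in blinded trials that measured renal function, and no injuries from testing or training in the last study (N = 28). These points stand, and they limit the size of the concern. They do not remove it, because the wording in both places is withdrawal from the study and the available text provides no later measurement.

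A reader might go further in four ways that the documents do not support.

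- **That the intention-to-treat promise cannot be kept.** For every outcome except the biopsy ones, a withdrawn person keeps baseline and 6-month values and can still be analysed in the randomised group. How the missing final value is handled may be set in an analysis plan that is not shown.
- **That about 11 of 80 would be lost to this rule (0.14 × 80 = 11.2).** The 14% is overall drop-out, most of which rewording Section C might not touch.
- **That training gains would be overstated by about 16% (24 against 24 × 0.86 = 20.6 Nm).** This is a single arm's mean, not a contrast between arms. It applies the overall drop-out rate and assumes that everyone lost had no gain.
- **That the arms would shed poor responders.** The triggers are safety findings. No efficacy result leads to removal, and neither does a low oxygen-consumption value.

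**Conclusion.** The concern holds in a limited form. Two rules in Section C allow withdrawal from the study on findings made after randomisation, Section D promises that all drop-outs enter an intention-to-treat analysis, and no available text connects the two by saying whether withdrawn people are still measured. On a plain reading their 12-month outcomes are missing, and for the biopsy outcomes nothing after baseline remains.

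The size is uncertain and may be small. The range of 0.3 to 3.8 Nm rests on assumed values of w and g and on all withdrawals falling in one arm. Equal withdrawal of similar people in both arms would largely cancel in the contrast. The upper end uses the entire planned drop-out allowance for this one cause. The point is worth acting on because the correction is cheap and cannot be made after the visits have been missed.

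**What to change.** Leave the reviewers' clinical judgement on stopping as it is. Reconcile Sections C and D by distinguishing two events: stopping training, supplement or both, and leaving follow-up. Suggested text for Section D, with a cross-reference at both rules in Section C:

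*A participant who stops training, supplement or both, for any reason, remains in follow-up unless he or she withdraws consent. The participant is invited to those 12-month assessments that the reviewing physician considers allowable, and is analysed in the group to which he or she was randomised. The date of and reason for stopping are recorded separately from any withdrawal of consent.*

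The cost is a wording change and a few final visits. Section B, Part II, already schedules these for every participant, although the documents show no budget for them. The gain is partial: some strength, exercise or biopsy tests may not be possible for a person stopped on safety grounds. DEXA, which the protocol describes as having no known risks, and the end-of-study blood sample may often remain feasible, subject to the physician's decision. Values still missing after that are for the analysis plan to handle.
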